#### Secondary analyses.

Secondary hypotheses explore relationships between somatosensory phenotype (QST clusters), genetic variants and nociceptor excitability signatures.

1. Somatosensory subgroup correspondence

- Compare microneurography variables across QST-defined phenotypic groups (sensory loss; mechanical hyperalgesia; thermal hyperalgesia) using non-parametric ANOVA (Kruskal–Wallis) or one-way ANOVA as appropriate.

- If omnibus tests are significant, perform post-hoc comparisons with correction for multiple testing.

2. Genetic variant effects

- Compare microneurography measures between participants who carry rare variants in ion channel genes (NaV, TRPA1) and those who do not, stratified by aetiology (diabetic versus non-diabetic).

- Use regression models to estimate the effect of genetic variants on fibre excitability, adjusting for confounders. If sample sizes for specific variants are small, present descriptive statistics and cautionary interpretation.

3. Microneurography association analyses

- Spearman rank-order correlations will evaluate associations between microneurography measures and clinical metrics: spontaneous pain intensity, evoked pain intensity, DN4/NPSI descriptor scores, and quality-of-life measures.

- A binomial regression model will examine the association between microneurography variables and membership of somatosensory subgroups.

Dimensionality reduction and clustering

Given the high dimensionality of clinical, genetic, microneurographic and biochemical data, we will use dimensionality reduction and unsupervised clustering to identify latent patient subgroups.

- Apply principal component analysis to standardised variables across the domains of interest (genetics, demographics, microneurography, biochemistry). Retain components that explain an adequate cumulative variance (e.g., eigenvalues >1).

- Apply k-means, centroid and hierarchical clustering on retained principal components. Determine optimal cluster number using multiple metrics (gap statistic, silhouette width, elbow method).

- After cluster assignment, compare original variables across clusters using omnibus tests with post-hoc comparisons to characterise cluster profiles.

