#### Quantitative sensory testing.

Quantitative sensory testing is a psychophysical technique used to assess sensory perception in response to defined stimuli. It provides a quantitative measure of sensory function and generates a sensory profile that captures both loss and gain of function across multiple sensory modalities. Quantitative sensory testing will be performed according to a modified version [42] of the German Research Network on Neuropathic Pain (DFNS) protocol [20,57]. In this study population, most participants are expected to experience bilateral symptoms; therefore, testing will be performed unilaterally on the dorsum of the foot and/or hand.

Quantitative sensory testing data will be entered into the Equista software package (version 1.2.2., CASQUAR GmbH), developed by the German Research Network on Neuropathic Pain. Equista converts raw data into z-scores, normalising results for age, sex, and the body region tested [58]. A z-score of zero represents the population mean, while scores greater than +2 or less than –2 standard deviations indicate gain or loss of function, respectively.

Participants will be stratified into somatosensory phenotype groups based on their quantitative sensory testing results. Two complementary approaches will be used:

Cluster analysis – An unbiased algorithm identifies three distinct phenotypic groups: sensory loss, mechanical hyperalgesia, and thermal hyperalgesia. Individuals will be assigned deterministically to one of these groups [13,19].Irritable versus non-irritable phenotype – Participants will be classified as having an irritable phenotype when detection thresholds are normal but there is evidence of sensory gain (mechanical or thermal hyperalgesia), or a non-irritable phenotype when there is either sensory loss or no evidence of sensory gain [59].

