#### Planned primary analysis.

Between-group comparisons (neuropathic pain vs no neuropathic pain) will be conducted using appropriate non-parametric tests (Mann–Whitney U test) where data are not normally distributed, or independent-samples t-tests where normality is satisfied.

Data from individual nociceptive fibres will be analysed with explicit consideration of clustering within participants. Where appropriate, fibre-level measurements will be summarised at the participant level (for example, by averaging) to provide an independent observation per participant for primary analyses. In addition, mixed-effects models will be used, with participant included as a random effect, to account for within-participant variability. Multiplicity arising from multiple outcomes will be addressed using appropriate multiple-comparison adjustments (for example, Bonferroni or false discovery rate correction).

This dual approach allows us to perform conservative primary analyses at the participant level by averaging, while also utilising more sophisticated modelling through a mixed-effects model that retains the detail of the individual fibre data while correcting for the dependence between fibres from the same participant. The mixed-effects model will bridge the participant (unit of inference) and individual fibre (unit of observation) without the statistical error of treating fibres from the same person as independent data points.

Multivariable logistic regression models will be used to examine the association between neuropathic pain status and microneurography-derived measures of axonal excitability and properties, adjusting for prespecified covariates (age, sex, diabetes status, neuropathy severity, and medication use).

Multicollinearity among predictors will be evaluated using variance inflation factors; when two predictors are highly correlated, the variable with greater variance or stronger biological relevance will be retained in the final model.

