#### Sample size justification.

Sample size calculations are based on power to identify differences in QST cluster frequencies and to support clustering and multivariate analyses.

- Using pilot quantitative sensory testing data from DOLORisk, expected cluster frequencies for diabetic distal symmetrical polyneuropathy are 53.9% (sensory loss), 25.0% (mechanical hyperalgesia) and 15.8% (thermal hyperalgesia). For non-diabetic neuropathies the corresponding frequencies are 49.7%, 21.2% and 14.5%.

- For moderate effects (Cohen’s d ~ 0.5) in the quantitative sensory testing cluster analyses, a total of 130 diabetic and 148 non-diabetic participants provides approximately 80% power at α = 0.05.

- For k-means and hierarchical clustering applied after principal component analysis, a conservative estimate requiring 2^8 = 256 participants was used to ensure adequate representation across variable permutations.

- A multivariate regression model with age, sex, diabetes status, neuropathy severity, and medication use will require 8 degrees of freedom to represent all its variables (assuming a categorical variable coding for 4 categories of medication). Allowing for at least 15 event per variable (EPV) we will require a sample size of at least 120 participants for model development. As described above, variable selection and filtering based on multicollinearity will likely increase the EPV.

- Taking these calculations together (and accounting for anticipated success rates in microneurography recordings: minimum 60% for diabetic participants and 80% for non-diabetic participants), the recruitment target is 272 participants (124 diabetic and 148 non-diabetic).

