#### Risk of bias and mitigation.

Potential sources of bias include misclassification of fibre type, sampling bias, outcome reporting bias and confounding.

Fibre classification bias will be minimised using pre-specified, reproducible criteria based on activity-dependent slowing of conduction velocity. Sampling bias will be reduced by recording from multiple receptive fields per participant and using mixed-effects models to account for within-participant variability. Confounders will be adjusted for in regression models. The protocol and statistical analysis plan will be pre-specified and published to minimise outcome reporting bias.

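### The QST-cluster comparison for secondary hypothesis 1 is fixed as a one-way test without covariates, so an age or sex difference between clusters could appear as a phenotype difference

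*Protocol article*

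**What the plan says.** All references are to the protocol article.

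- **Secondary analyses, item 1** (somatosensory subgroup correspondence): "Compare microneurography variables across QST-defined phenotypic groups (sensory loss; mechanical hyperalgesia; thermal hyperalgesia) using non-parametric ANOVA", with one-way ANOVA as the alternative. Corrected post-hoc comparisons follow only a significant omnibus test. No covariate or stratum is named.
- **Secondary analyses, item 2** (genetic variants): the comparison is "stratified by aetiology (diabetic versus non-diabetic"), and its regression models adjust for confounders.
- **Secondary analyses, item 3**: "A binomial regression model will examine the association between microneurography variables and membership of somatosensory subgroups". No covariates are listed.
- **Planned primary analysis**: the logistic model is fitted "adjusting for prespecified covariates (age, sex, diabetes status, neuropathy severity, and medication use").
- **Risk of bias and mitigation**: "Confounders will be adjusted for in regression models".
- **Quantitative sensory testing**: the software turns raw values into z-scores, "normalising results for age, sex, and the body region tested". No such step is stated for microneurography measures.
- **Microneurography**: above 70 years, or in severe neuropathy, where the superficial peroneal nerve is denervated or cannot be reached, recording moves to the superficial radial nerve or a more proximal peroneal site.
- **Sample size justification**: for effects of about d = 0.5 in the QST cluster analyses, "a total of 130 diabetic and 148 non-diabetic participants provides approximately 80% power" at alpha 0.05.

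**The concern.** Item 1 is the named test of secondary hypothesis 1, that somatosensory subgroups match nociceptor properties. Its groups are observed, not allocated, so they can differ in age and sex. The QST values that define the groups have age and sex removed. The outcomes compared across them have not, and the place where the outcome is measured can itself depend on age and severity. A one-way test cannot separate these influences from sensory phenotype, and its result decides whether post-hoc comparisons are made at all.

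This is a choice of method that the article fixes, not a detail left open. Kruskal-Wallis has no place for a covariate, and a one-way ANOVA has none by definition. An analysis plan that follows the text inherits the gap. The article's own standard elsewhere is higher: age, sex and diabetes status are prespecified covariates in the primary logistic model, and the genetic comparison is both stratified and adjusted.

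**Working it through.** **1. The plan's own figure.** Inputs from Sample size justification: d = 0.5, two-sided alpha 0.05, cluster frequencies 53.9/25.0/15.8% (130 diabetic) and 49.7/21.2/14.5% (148 non-diabetic). The contrast is not named. Taking sensory loss against the two hyperalgesia clusters combined, power = Φ(0.5/√(1/n₁ + 1/n₂) − 1.96):

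- Diabetic, 70.1 v 53.0: Φ(2.747 − 1.96) = 78.4%.
- Non-diabetic, 73.6 v 52.8: Φ(2.772 − 1.96) = 79.2%.

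Both are close to the stated 80%, so the numbers appear to have been set within each aetiology. The contrast is inferred.

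**2. Evaluable numbers.** The recruitment target and the minimum recording success rates give 0.6 × 124 = 74.4 diabetic and 0.8 × 148 = 118.4 non-diabetic, about 193 in all. Using the stated frequencies, the clusters hold about 99 (sensory loss), 44 (mechanical hyperalgesia) and 29 (thermal hyperalgesia), 172 in total.

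**3. False positives from an age difference.** Assumptions, since the documents give neither quantity: correlation r between age and the measure is 0.2 to 0.5, the sensory-loss cluster is g = 0.2 to 0.5 SD older, and there is no true cluster effect. The spurious shift is δ = r × g. The one-way F test then has non-centrality λ = (99 × 73/172) × δ² = 42.0 × δ² on 2 and 169 degrees of freedom.

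| r | g | δ (SD) | λ | Rejection rate, unadjusted |
|---|---|---|---|---|
| 0.2 | 0.2 | 0.04 | 0.07 | 5.5% |
| 0.3 | 0.3 | 0.09 | 0.34 | 7.6% |
| 0.4 | 0.5 | 0.20 | 1.68 | 19.2% |
| 0.5 | 0.5 | 0.25 | 2.63 | 28.1% |

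Simulation agrees. For r = 0.2 to 0.4 with these cluster sizes it gives 5.3% to 19.2%. For r = 0.3 to 0.5, with 192 participants all placed in a cluster and a 0.5 SD aetiology difference, it gives about 7% to 29%. With an age term the rate is about 5% throughout. Sex was not simulated; the same mechanism applies if the sexes differ both in cluster membership and in the measure.

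**4. Aetiology as a confounder.** At the planning numbers the diabetic share of the three clusters is 70.1/(70.1 + 73.6) = 48.8%, 32.5/(32.5 + 31.4) = 50.9% and 20.5/(20.5 + 21.5) = 48.9%. These differ by about 2 points, so a 1 SD aetiology effect would bias a cluster contrast by about 0.02 SD.

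**5. Power.** For sensory loss against combined hyperalgesia with evaluable numbers, pooling gives 89.9% (98.9 v 72.6), against 54.7% in diabetic and 69.8% in non-diabetic participants analysed separately. Adjustment divides the residual variance by 1/(1 − R²). For sensory loss against mechanical hyperalgesia (t-test; 98.5 v 43.5, from 74 and 118 whole participants):

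| Covariate R² (assumed) | 0 | 0.05 | 0.10 | 0.20 | 0.30 |
|---|---|---|---|---|---|
| Power | 77.9% | 79.9% | 82.0% | 86.2% | 90.3% |

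The gain is about 2 to 12 points. A 0.5 SD aetiology difference alone is R² of about 0.06, worth about 2 points.

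**The case against.** The strongest reply is that an adjusted route already exists. Item 3 plans a binomial regression linking microneurography variables to subgroup membership, and the section on bias says that regression models adjust for confounders. Covariate lists for secondary models are commonly left to an analysis plan, which is not shown here. This stands in part: a reader might infer that the cluster question has no adjusted analysis, and the article does not support that. But the regression models membership rather than the microneurography measure, its covariates are not named, and it does not replace the omnibus test that decides on post-hoc comparisons.

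Three other points stand.

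- A reader might infer that combining the aetiologies wastes power because the numbers are stated by aetiology. It does not: step 5 shows that pooling raises power over separate analyses. That item 1 is pooled is itself only inferred from the absence of a stratum. Patient stratification says in general terms that participants will be grouped by aetiology.
- A reader might infer that unequal diabetic shares bias the comparison. On the article's own frequencies they are nearly equal.
- Clusters built from age- and sex-normalised z-scores should be less related to age than clusters built from raw values. This makes the low end of the range more plausible, but does not guarantee balance among the participants who yield a recording.

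The secondary hypotheses are also described as exploratory in nature, which limits the weight of the point.

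**Conclusion.** The point holds for confounding by age and, by the same reasoning, sex. The article fixes an unadjusted test for a named secondary hypothesis in non-randomised groups, with normalisation on one side only and a recording site that can vary with age or severity. The false-positive rate could lie anywhere from about 5% to 29%, against about 5% with an age term. At the low end the inflation is negligible. The range rests wholly on the assumed age gap and correlation, so it shows what is possible and is not an estimate of what will happen.

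The power argument is secondary: about 2 to 12 points for sensory loss against mechanical hyperalgesia, only relative to a covariate-adjusted pooled model, and only at the assumed R² of 0.05 to 0.30. Diabetes status belongs in the model for precision; on the stated frequencies it removes almost no bias. The change is worth making because it is cheap and can be made before analysis, with data collection running to September 2029.

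**What to change.** Make the main analysis for item 1 a linear model, on a rank-transformed outcome where needed, of each participant-level microneurography measure on QST cluster, with age, sex, diabetes status and recording site as terms. Base both the omnibus test and the post-hoc comparisons on that model. Keep Kruskal-Wallis or one-way ANOVA as a descriptive, unadjusted result, and list the same covariates for the binomial regression in item 3. Leave neuropathy severity out of the main version, because sensory loss helps to define the clusters.

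Report cluster-by-aetiology estimates only as exploratory: with 74 evaluable diabetic participants, 15.8% gives about 12 with thermal hyperalgesia.

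The cost is wording in the analysis plan, a few degrees of freedom and slightly more analysis work. Age, sex (recorded as gender in the questionnaire section) and diabetes status are already collected, and the recording site is known for each session.

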Abnormal excitability and activity of peripheral nociceptor fibres appear to drive pain in a subset of people with chronic neuropathic pain [14,15]. Both human and animal studies link neuropathic pain to peripheral neuronal hyperexcitability, and human studies indicate that peripheral nociceptor input can maintain neuropathic pain. For example, topical or systemic lidocaine reduces spontaneous neuropathic pain and mechanical and thermal hypersensitivity in patients with peripheral nerve injury or distal symmetrical polyneuropathy [16]. Pre-clinical models implicate altered expression and gating of voltage-gated sodium channels (NaV) in injured nociceptive fibres as mechanisms for hyperexcitability [14]. Human genetic studies corroborate these findings. For example, rare gain- or loss-of-function mutations in nociceptor channels (e.g., TRPA1, NaV subtypes) cause extreme pain syndromes or insensitivity to pain [5,17]. While variants in the same genes are linked to more common neuropathies such as diabetes and small-fibre neuropathy [10,18]. Investigation of rare genetic variants provides important clues to the molecular mechanisms of neuropathic pain. Measuring nociceptive fibre activity directly can identify those whose pain is driven primarily by peripheral fibre hyperexcitability, thereby uncovering key pathophysiological processes and guiding targeted therapy.

However, human studies have not fully characterised which nociceptor populations are abnormal, how neuronal abnormalities relate to clinical phenotype, or the precise molecular changes involved. Many attempts have stratified patients by clinical and sensory profiles, for example via quantitative sensory testing. [19]. Quantitative sensory testing is a standardised and validated psychophysical tool for the systematic assessment and quantification of an individual's pain perception by applying controlled stimuli to areas of pain [20]. This helps in the objective evaluation of pain conditions and responses. But, these sensory profiles have not been tightly linked to direct measures of nociceptor activity. Surrogate neurophysiological measures such as, large-fibre axonal excitability, do not reliably differentiate painful from painless neuropathies [21]. Direct recordings from nociceptors are therefore essential.

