Microneurography is the only neurophysiological tool that records neuronal activity directly from nerve fibres in awake humans [22]. It allows assessment of thin myelinated Aδ and unmyelinated C-fibres (largely composed of nociceptive fibres), which cannot be assessed by conventional nerve conduction studies nor axonal excitability [23]. It is thus ideally suited to investigate peripheral mechanisms underlying neuropathic pain [24,25]. Microneurography studies have shown nociceptor hyperexcitability in pathological states including diabetes and individuals with NaV channel mutations [26–37]. For example, certain NaV1.7 pathogenic variants increase spontaneous activity in previously “silent” nociceptors, whereas other NaV1.8 variants reduce spontaneous firing, demonstrating variant-specific effects across nociceptor subtypes [38–40]. This opens the possibility of personalised, mechanism-targeted treatments.

Nevertheless, it remains unclear how nociceptor populations are affected across different painful neuropathies, how neuronal excitability correlates with clinical and sensory phenotypes, and which molecular mechanisms underlie these changes. This study will investigate these questions.

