### Study participants

Healthy: adults (≥16 years) without risk factors or clinical features of peripheral neuropathy.

Patient participants: adults (≥16 years) with risk factors for neuropathy (for example diabetes), symptoms suggestive of neuropathy, or a diagnosis of diabetic or non-diabetic peripheral neuropathy, including small-fibre neuropathy, established by clinical assessment and investigations. Also included are patients (or their first-degree relatives) with clinical features or a confirmed diagnosis of paroxysmal extreme pain disorder, familial episodic pain syndrome, erythromelalgia, or congenital insensitivity to pain.

Exclusion criteria: pregnancy; insufficient English or impaired capacity preventing informed consent or completion of questionnaires; severe psychiatric illness; significant pain from other causes that would confound assessment; central nervous system lesions likely to complicate somatosensory testing; or any other reason the investigator deems the participant unsuitable.

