#### Study hypotheses.

The primary hypothesis is that participants with neuropathic pain will exhibit altered axonal properties and excitability compared to those without neuropathic pain.

Secondary hypotheses we will test are:

1) Somatosensory subgroups will match nociceptor properties. The planned outcomes are comparisons between neurophysiological and sensory phenotype variables, for example, mechanical hyperalgesia sensory profile will show lowered neurophysiological threshold to mechanical stimulation.2) Genetic variants will confer a unique nociceptive axonal profile and excitability signature. The planned outcome is the comparison of nociceptor fibre excitability and axonal properties between those participants with and without genetic variants.

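### The genetic comparison pools all rare NaV and TRPA1 carriers against non-carriers, although the protocol says such variants act in opposite directions, so real effects can be diluted or, with a balanced mix, cancelled

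*Protocol article*

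**What the plan says.** Study hypotheses defines the planned outcome for secondary hypothesis 2 as a "comparison of nociceptor fibre excitability and axonal properties between those participants with and without genetic variants". Secondary analyses, item 2, turns this into a comparison of "participants who carry rare variants in ion channel genes (NaV, TRPA1) and those who do not, stratified by aetiology (diabetic versus non-diabetic". Diabetes status is the only stratifier named.

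A second bullet in item 2 adds confounder-adjusted regression for the effect of variants. Where numbers for specific variants are small, it falls back on descriptive statistics and cautious interpretation. How variants enter the regression is not stated.

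The Introduction describes the direction of effect. It says that "rare gain- or loss-of-function mutations in nociceptor channels (e.g., TRPA1, NaV subtypes) cause extreme pain syndromes or insensitivity to pain". On microneurography it says that "certain NaV1.7 pathogenic variants increase spontaneous activity in previously “silent” nociceptors", while "other NaV1.8 variants reduce spontaneous firing, demonstrating variant-specific effects across nociceptor subtypes".

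Both ends of the spectrum are eligible. Study participants lists "paroxysmal extreme pain disorder, familial episodic pain syndrome, erythromelalgia, or congenital insensitivity to pain" and also admits first-degree relatives. Patient stratification places these conditions, including insensitivity to pain, in a fourth group called extreme pain phenotypes.

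**The concern.** Hypothesis 2 proposes that genetic variants confer a distinctive excitability signature. The contrast named to test it is one difference in means between all carriers and all non-carriers. If some carriers have raised and others lowered values of the same measure, that difference is a weighted average of opposite effects. It also depends on which variants happened to be recruited. The clearest example is spontaneous activity: Primary outcome comparisons lists it as a study measure, and the Introduction names it as moving in both directions.

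Two things are at stake. A null pooled result could be read as showing that variants do not matter when they do. A positive pooled result would not say which gene or direction produced it.

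**Working it through.** The article gives no sample size, power, carrier count or effect size for the genetic comparison, so there is no stated figure to reproduce. What follows is an illustration.

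**Inputs from the article**
- Non-diabetic target 148 and minimum microneurography success 80% (Sample size justification): 148 × 0.80 = 118.4, taken as 118 usable.
- Two-tailed tests (Statistical plan). α = 0.05, which the article states only for the sensory-testing cluster calculation.

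**Assumptions, not in the article**
- 20 carriers, leaving 118 − 20 = 98 non-carriers.
- Each carrier's mean is shifted by +d or −d, with SD 1 within each direction. A share q has the opposite direction.

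**Formulas**
- Pooled mean difference = d(1 − 2q).
- Variance among carriers = 1 + 4q(1 − q)d².
- SE = √[(1 + 4q(1 − q)d²)/20 + 1/98].
- Power is the two-sided normal approximation at ratio = difference/SE.

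**Pooled contrast, d = 0.8**

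| Opposite share q | Difference | SE | Ratio | Power |
|---|---|---|---|---|
| 0 | 0.80 | 0.245 | 3.26 | 0.90 |
| 10% | 0.64 | 0.268 | 2.39 | 0.67 |
| 25% | 0.40 | 0.290 | 1.38 | 0.28 |
| 50% | 0 | 0.304 | 0 | 0.05 |

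**Direction-specific contrast at 50:50, d = 0.8**

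There are 10 carriers each way against 98 non-carriers. SE = √(1/10 + 1/98) = 0.332 and the ratio is 0.8/0.332 = 2.41. Power is 0.67 per direction at α = 0.05. With Bonferroni for two tests (α = 0.025 each) it is 0.57.

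**Sensitivity to d (20 carriers, 98 non-carriers)**
- d = 1: pooled 0.98 with one direction, 0.82 at 10% opposite, 0.36 at 25%, 0.24 at 30%, 0.05 at 50:50. Split at 50:50: 0.85, or 0.78 after Bonferroni.
- d = 0.5: pooled 0.53, 0.35 and 0.16 at 0, 10% and 25% opposite, and 0.05 at 50:50. Split at 50:50: 0.33 unadjusted.

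**Wider range**

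This covers 10 to 30 carriers, d from 0.5 to 1.0, and 118 usable non-diabetic or 74 usable diabetic participants (124 × 0.60 = 74.4). Pooled power runs from 0.31 to 1.00 with one direction, from 0.11 to 0.47 at 25% opposite, and is 0.05 at 50:50.

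**The case against.** The strongest reply is that the pooled contrast is not the only genetic analysis. The fallback for specific variants makes sense only if variants are looked at individually where numbers allow. This stands: a reader might infer that everything rests on one pooled test, and the article does not say so. It does not remove the problem. The bullet fixes no grouping by gene or direction, and where numbers are small it offers description only. Functional direction lies between one pooled group and single variants, and it is the level at which a test may be feasible.

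A second reply is that variant coding belongs in the analysis plan, which is not shown, and that this is an exploratory, unpowered hypothesis. An unseen plan may indeed define the coding. But the binary contrast is stated in two places here, so the point concerns a stated choice and not an omitted detail.

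A third reply is that cancellation is not shown. That also stands. A zero difference needs roughly balanced, equal and opposite effects on the same measure, and the carrier mix is unknown. With few opposite-direction carriers the loss is moderate. Splitting also has a price: multiplicity adjustment, and variants of unknown direction that shrink both groups.

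Two further inferences are tempting but unsupported:
- **Stratum.** A reader might conclude that nearly all inherited syndromes fall into the non-diabetic stratum and are compared there with acquired neuropathy. Patient stratification sets the extreme phenotypes apart as a fourth group, so non-diabetic in item 2 may mean the third group only. The article does not settle which.
- **Relatives.** A reader might conclude that ignoring kinship makes intervals too narrow. No number of relatives is given, and the direction can reverse: when a carrier is compared with a non-carrier relative, positive family correlation makes unadjusted intervals too wide.

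**Conclusion.** The point holds as a risk of dilution, with cancellation as the limiting case. The named contrast conflicts with the article's own account of how these variants act, and it suits a hypothesis about distinctive signatures poorly.

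Under the assumed 20 against 98 with effects of 0.8 SD, power falls from 0.90 to 0.28 when a quarter of carriers act in the opposite direction, and to 0.05 at an even mix. At that even mix, testing by direction recovers about 0.57 to 0.67 per direction, depending on multiplicity adjustment. These figures rest entirely on assumed carrier numbers, mix and effect sizes, and on every variant's direction being known. They show how the loss behaves and do not predict it for this study.

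The documents do not support saying that effects will cancel, that pooling is the only genetic analysis, that the non-diabetic stratum is mis-specified, or that intervals will be too narrow.

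**What to change.** 1. Before genetic data are linked to microneurography results, class each variant by gene and functional direction: gain, loss or uncertain.
2. Make the comparison of each direction with non-carriers the main analysis for hypothesis 2, with the multiplicity adjustment that Statistical plan already foresees. Keep the pooled contrast as descriptive at most.
3. State that the extreme-phenotype group (group iv in Patient stratification) is reported separately from carriers found among diabetic and non-diabetic neuropathy.
4. Where relatives are included, account for family membership with a family random effect or family-clustered standard errors.

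The cost is revised analysis wording and annotation of sequencing that Genotyping already plans. Recruitment and data collection run to September 2029, so there is time. The downside is smaller groups, some only descriptive (which item 2 already allows), and some variants left as uncertain.
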